## **2 Study Design**

### **2.1 Study Overview**

The objective of this study was to assess the effects of acupoint hot compress during early puerperium on parturients after a vaginal delivery.

### **2.2 Background**

Early puerperium is the period of adjustment after delivery, which extends until the first week postpartum. It is recommended that mothers and newborns should receive care within 24 hours after birth as recommended by the World Health Organization guidelines for postnatal care, and this includes the assessment of micturition, urinary incontinence and bowel function, healing of any perineal wounds, fatigue, pain, uterine tenderness and lochia, and improving the breastfeeding progress and emotional well-being. These issues can interfere with a woman's ability to care for herself and her infant. Moreover, maternal self-care needs, already in the first few days after delivery, go beyond the mother's

physical health as it extends to the mother's emotional well-being as well.

Hot compresses have proved to be an effective complementary treatment for myofascial pain syndrome in the upper trapezius muscle, and they have exhibited an extraordinary capability for the pressure pain threshold and in improving the quality of life. Warm compress bstage intervention was found to significantly reduce the intensity of pain the day after delivery. Acupoint hot compress, with a combination of acupoints and natural physical agent heat, is more acceptable, both physically and mentally, for puerperal patients and their families, due to its noninvasive feature. However, the effects of acupoint hot compress for patients during the early puerperium remain uncertain due to a lack of evidence-based support from clinical trials.

## **2.3 Materials and methods**

### **2.3.1 Objectives**

The trial is designed to evaluate whether acupoint hot compress involving the abdominal, lumbosacral and plantar regions could reduce the incidence of postpartum urinary retention, relieve postpartum uterine contraction pain, prevent emotional disorders, and promote lactation.

### **2.3.2 Trial registration**

The final protocol version is 2.1, dated 25 August 2020. The protocol was approved by the Ethics Committee of Women's Hospital, School of Medicine, Zhejiang University with the Approval No. IRB-20200223-R on 7 September 2020. The trial was registered at World Health Organization International Clinical Trial Registration Platform, Chinese Clinical Trial Registry (Chictr) with the registration number ChiCTR2000038417. Registered 22 September 2020, <http://www.chictr.org.cn/showproj.aspx?proj=57108>.

### **2.3.3 Trial design**

The study is a prospective, multi-center, and randomized controlled clinical trial, which will be conducted in China. All enrolled subjects will be comprehensively briefed on the study, including the purpose, procedure, and possible risks of the study. Informed consent will be obtained from all participants before the start of this study. The demographic data, information about pregnancy, delivery, and newborns will be recorded as baseline data. When the protocol need to be modified, the implementation will be started only after the corresponding revised parts approved by the ethics committee, and all research centers, investigators and the funder are notified at the same time. The study will follow the Code of Ethics of the World Medical Association (Declaration of Helsinki). This protocol is compliant with the Standard Protocol Items: Recommendations for Interventional Trials (SPIRIT) statement (Figure 1) and the Consolidated Standards of Reporting Trials (CONSORT) guidelines (Figure 2).

|                                                    | STUDY PERIOD |            |                               |                      |                      |                               |                                |                                |                                |
|----------------------------------------------------|--------------|------------|-------------------------------|----------------------|----------------------|-------------------------------|--------------------------------|--------------------------------|--------------------------------|
|                                                    | Enrolment    | Allocation | Post-allocation               |                      |                      | Follow-up                     |                                |                                |                                |
| TIMEPOINT
(after delivery)                      | - $t_1$      | 0          | $t_1$
Within 30
minutes | $t_2$
24
hours | $t_3$
48
hours | $t_4$
6 $\pm$ 0.5
hours | $t_5$
28 $\pm$ 0.5
hours | $t_6$
52 $\pm$ 0.5
hours | $t_7$
76 $\pm$ 0.5
hours |
| ENROLMENT                                   |              |            |                               |                      |                      |                               |                                |                                |                                |
| Eligibility screen                                 | X            |            |                               |                      |                      |                               |                                |                                |                                |
| Informed consent                                   | X            |            |                               |                      |                      |                               |                                |                                |                                |
| Randomization                                      | X            |            |                               |                      |                      |                               |                                |                                |                                |
| Allocation                                         |              | X          |                               |                      |                      |                               |                                |                                |                                |
| INTERVENTIONS                               |              |            |                               |                      |                      |                               |                                |                                |                                |
| Routine postpartum care &
Acupoint hot compress |              |            | X                             | X                    | X                    |                               |                                |                                |                                |
| Routine postpartum care                            |              |            | X                             | X                    | X                    |                               |                                |                                |                                |
| ASSESSMENTS                                 |              |            |                               |                      |                      |                               |                                |                                |                                |
| Postpartum urinary retention                       |              |            |                               |                      |                      | X                             |                                |                                |                                |
| Postpartum uterine contraction pain (VAS)          |              |            |                               |                      |                      | X                             | X                              | X                              | X                              |
| Emotion symptoms(EPDS)                             |              |            |                               |                      |                      |                               |                                |                                | X                              |
| Lactation                                          |              |            |                               |                      |                      |                               | X                              | X                              | X                              |

**Figure 1. The schedule of enrolment, interventions, and assessments**

[figure not shown]

**Figure 2. Trial flow chart**

## 2.3.4 Recruitment

The study will be conducted in 12 hospitals in China: Women's Hospital, School of Medicine, Zhejiang University; Tongde Hospital of Zhejiang Province; Yiwu Maternity and Child Health Care Hospital; Jiaxing Maternity and Child Health Care Hospital; Zhejiang Xiaoshan Hospital; Zhoushan Women and Children Hospital; Shaoxing Maternity and Child Health Care Hospital; The Women & Children Hospital of Dongyang; Ruian People's Hospital; Cixi Maternity and Child Health Care Hospital; Wenling Maternity and Child Health Care Hospital and Xianju People's Hospital. Posters will be placed in each institution's bulletin board to recruit subjects. No specific culture, race, or socio-economic group will be targeted or restricted from the recruitment.

## 2.3.5 Participants

### 2.3.5.1 Inclusion criteria

- (1) Age is more than 18 years;
- (2) Nulliparous women with a singleton pregnancy;
- (3) Gestational age of delivery is 37 - 42 weeks;
- (4) Parturient undergoing vaginal delivery;
- (5) Breastfeeding;
- (6) Provision of the signed informed consent.

### 2.3.5.2 Exclusion criteria

- (1) Termination of pregnancy due to fetal malformation or stillbirth;
- (2) Family history of mental illness or tumor;
- (3) Mental and psychological diseases, traumatic events, or communication barriers;

- (4) Pre-pregnancy central nervous system diseases, internal and surgical diseases, breast dysplasia, urogenital related diseases, infectious diseases, and long-term drug treatment;
- (5) Skin damage, ulceration, sensory disorders, acute closed injury, suppurative infection, acute inflammation and other infectious diseases, skin diseases, severe diabetes, high fever and allergy to product materials;
- (6) Incomplete provision of information.

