### **2.3.5.4 Subject drop-out and discontinuation**

- (1) Implementation of rescue due to postpartum hemorrhage, eclampsia, or other obstetric conditions;
- (2) Change of vaginal delivery to cesarean section;
- (3) Infection during delivery;
- (4) Indwelling catheter and the need to use diuretics due to disease within 6 hours after delivery;
- (5) Degree III laceration above the perineal fissure;
- (6) Neonatal transfer after birth;
- (7) The investigator can terminate the subject from continuing the clinical trial at any stage, if the investigator deems that the risks of continuing the clinical trial outweigh the benefits;
- (8) Subject's poor compliance to this trial.

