### **2.6.2 Intervention group**

In addition to routine postpartum care, the participants in the intervention group were administered a 4-hour acupoint hot compress with a constant temperature of  $45\pm 2^{\circ}\text{C}$  within 30 minutes after delivery (Intervention I), 24 hours after delivery (Intervention II), and 48 hours after delivery (Intervention III).

As seen in Figure 3, for Intervention I, two hot cores (Model A) were administered on Shenque (RN8, in the center of the umbilicus) and Baliao (BL31-34, in the region of the sacrum, between the posterior-superior iliac spine and the posterior midline, in the 1st, 2nd, 3rd and 4th posterior sacral foramen, from the top to the bottom are Shangliao, Ciliao, Zhongliao, and Xialiao). Two hot cores (Model B) were bilaterally administered in Yongquan (KI1, on the sole, in the depression when the foot was in plantar flexion, and in the anterior depression when the foot was flexed, approximately at the junction of the anterior 1/3 and posterior 2/3 of the sole). During Interventions II and III, only one hot core (Model A) was administered on Shenque (RN8). The selection of acupoints is based on the clinical experiences of our hospital and the consultation with 10 experts in Chinese medicine. The location of the involved acupoints is described as per the Nomenclature and Location of Acupuncture Points (National Standard of People's Republic of China, 2006 [GB/T 12346-2006]).

[figure not shown]

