## 2.7 Baseline data

Baseline information includes: Age; BMI(Prepregnancy); Race; ABO blood groups; Rh blood types; Place of residence; Educational level; Occupation category; History of tobacco consumption; History of alcohol intake; Insurance; Age of menarche; Menstrual cycle; Menstrual phase; Dysmenorrhea; Marital status; Couple relationship; Mode of conception; Prenatal care; Pregnancy complications; Fetus and appendages; Gestational age of delivery; BMI(Predelivery); Sleep duration per day; Trouble falling asleep; Appetite; Little interest or pleasure in doing things; Feeling down, depressed, or hopeless; Feeling nervous, anxious or on edge; Not being able to stop or control worrying; Labor induction; Augmentation by oxytocin; Rupture of membranes; Spinal analgesia for labor pain; Duration of labor stages; Perineum conditions; Assisted vaginal delivery; Placenta delivery method; Completeness of placenta; Fetal membranes; Curettage; Uterotonics drugs; Bowel movement during labor; Newborn weight; Newborn length; Apgar score; Time between birth and early sucking of newborns; Knowledge of breastfeeding; Postpartum diet within 28 hours after delivery; Postpartum diet during 52-76 hours after delivery; Postpartum appetite within 28 hours after delivery; Postpartum appetite during 28-52 hours after delivery; Postpartum appetite during 52-76 hours after delivery.

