## 2.9 Safety Evaluation

The medical device for hot compress used in the present study is licensed by Medical Products Administration (Jiangxi Province, China) with a Licensed Number 20192090292. No adverse events (AEs) have been reported. In the present study, the safety evaluation will be comprehensively conducted and followed. In the study, the participants with sensory disorders have been excluded. Prior to obtaining consent from the participants, the potential AEs have been explained to the participants in detail. AEs will be monitored and recorded in detail throughout the whole study period.

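### The protocol excludes women with impaired sensation but screens for it only at enrolment, apparently before delivery, and shows no sensation check before the first 4-hour heat session, although women with spinal labour analgesia are enrolled

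*Supplement*

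**What the plan says.** **The safeguard.** Protocol 2.3.5.2, criterion (5), lists "Skin damage, ulceration, sensory disorders, acute closed injury" with other skin, infectious and allergic conditions. It gives no definition, test, body site or time of assessment. Section 2.9 relies on it: "In the study, the participants with sensory disorders have been excluded".

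**Its timing.** In the Figure 1 schedule (2.3.3), "Eligibility screen" is marked in the enrolment column only, ahead of allocation and of the first session. The same section says "Informed consent will be obtained from all participants before the start of this study". The discontinuation reasons in 2.3.5.4 include "Change of vaginal delivery to cesarean section" and infection during delivery.

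**The exposure.** Section 2.6.2 gives the intervention arm a 4-hour compress at 45±2°C, starting within 30 minutes of delivery, at the umbilicus, the sacrum and both soles. The second and third sessions, at 24 and 48 hours, heat the umbilicus only.

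**The women exposed.** "Spinal analgesia for labor pain" is a baseline variable (2.7). It is neither an exclusion nor a discontinuation reason. SAP 9 says that spinal analgesia may affect the outcomes and gives this as the reason for the labour-analgesia subgroup in SAP 7.

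**The concern.** By excluding sensory disorders, the protocol itself treats impaired sensation as a reason not to use this device. A woman who has had spinal labour analgesia may still have reduced sensation in the lower body shortly after delivery, when the first and most extensive session begins. A screen completed before delivery could not pick that up. If nobody checks again, heat could stay in place for 4 hours on skin where she may not notice that it is too hot.

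What is at stake is avoidable harm to participants. The authors considered spinal analgesia for its effect on outcomes, but nothing shown considers it for heat safety.

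**Working it through.** The plan gives no figure for this risk, so the first step is a comparison of the text. The arithmetic that follows prices the remedy and does not measure the hazard.

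**1. Text side by side**

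| Question | Where | What is found |
|---|---|---|
| Is impaired sensation treated as a hazard? | 2.3.5.2 (5), 2.9 | Yes, but undefined |
| When is it judged? | Figure 1 | At enrolment only, not repeated |
| Is enrolment before delivery? | 2.3.5.4 (2), (3) | Implied: conversion to caesarean and infection during delivery are reasons to leave after enrolment |
| Are women with spinal analgesia enrolled? | 2.7, SAP 9 | Yes |
| Is sensation checked before heat, or heat deferred? | 2.6.2, 2.9 | Nothing shown |
| Does a discontinuation reason concern sensation? | 2.3.5.4 (1)–(8) | None of the eight; (7) is general investigator discretion |

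The gap does not depend wholly on pre-delivery screening. Even if some women were screened after birth, nothing ties the criterion to the moment of application.

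**2. Room to defer**

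Inputs: latest planned start 0.5 h and session length 4 h (2.6.2); first-urination cut-off 6.5 h (2.8.1).

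- Planned end: 0.5 + 4 = 4.5 h, leaving 6.5 − 4.5 = 2.0 h.
- Latest start for a full session before the cut-off: 6.5 − 4 = 2.5 h.
- Heat before the cut-off for a start at s hours: min(4, 6.5 − s). At s = 3.5 this is 3 h (75%); at s = 4.5 it is 2 h (50%).

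The cut-off governs only the first-urination part of the endpoint. The catheter part runs to 72 hours.

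**3. Worst-case dilution**

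Inputs: pilot rates 7.7% and 25.7%, one-sided α = 0.025, 600 per arm and 20% drop-out (2.4). That leaves 600 × 0.8 = 480 per arm. Suppose a share f of the intervention arm gets no benefit at all and so has the control rate. The values of f are assumptions.

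Intervention rate = 7.7% + f × (25.7% − 7.7%). Power is from the two-proportion z test with pooled null variance. The last column assumes that the two centres dropped in protocol section 11 (1) are among the 12 listed in 2.3.4, which gives 10 × 50 × 0.8 = 400 per arm.

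| f | Intervention rate | Difference (points) | Power, 480 per arm | Power, 400 per arm |
|---|---|---|---|---|
| 10% | 9.5% | 16.2 | >99.9% | >99.9% |
| 20% | 11.3% | 14.4 | >99.9% | >99.9% |
| 30% | 13.1% | 12.6 | 99.9% | 99.5% |
| 50% | 16.7% | 9.0 | 92.8% | 87.7% |

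At the pilot rates, power stays above the planned 80% in every row.

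**The case against.** **The hazard is not shown in the documents.** They give no drug, dose, block level, share of users or burn data. Section 2.9 says that the device is licensed and that no adverse events have been reported, and section 4 says the same of previous studies and practice. This stands as a limit on size. But neither section says whether that experience included women with spinal analgesia heated within 30 minutes of delivery.

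**Pre-delivery screening is inferred.** The inclusion criteria require breastfeeding and refer to gestational age at delivery, which point nearer to birth or after it. Criterion (5) also lists passing states such as high fever, so staff could read it as a device contraindication list to apply when placing the patch. The flow chart is not shown. This stands, and it is why the heading says apparently. Such a reading is possible, but it is not written down, and sites may differ.

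**The women are not unattended.** They receive routine postpartum observation (2.6.1), adverse events are monitored throughout (2.9), subjects can call the researcher (section 4), and the investigator may stop participation on risk grounds (2.3.5.4 (7)). Section 6 mentions a standard procedure that is not shown and may contain the check. All true, but none of the text shown is a sensory check.

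**Safety tables.** A reader might infer that SAP 8 is deficient because it summarises events by arm and not by analgesia. The documents do not support that: individual listings are planned and analgesia is recorded, so an event can be matched. A cross-tabulation is optional.

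**Conclusion.** The point holds as a gap in the protocol text, and it should be fixed. The protocol names impaired sensation as a contraindication, enrols women in whom it may be present for a time after delivery, and does not require the criterion to be checked when heat is applied. Confidence is medium, because the timing of the screen is inferred and the site procedure is not shown.

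The size of the risk cannot be estimated: the documents give neither the share of women with spinal analgesia nor how often reduced sensation remains at 30 minutes.

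Two stronger readings are tempting. One is that women were in fact heated on numb skin or burned; nothing in the documents shows this. The other is that the primary result is biased; the estimate and its test are not affected by the missing check.

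**What to change.** **In 2.6.2, with a cross-reference in 2.3.5.2 (5):**
- Re-apply the sensory criterion at each heated site immediately before the first session.
- Defer or omit heat at any site where sensation is reduced.
- Record the actual start time and any site omitted.

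**On analysis status:** state that such deferral or omission is neither "Subject's poor compliance to this trial" (2.3.5.4 (8)) nor a protocol deviation. The woman then stays in her randomised arm in the intention-to-treat analysis of SAP 1 and in any per-protocol analysis. The second half matters because section 11 (2) of the protocol describes the analysis as per protocol. If that governed and late or partial heat counted as a deviation, women could be removed from the intervention arm only, and selectively those with analgesia.

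**Optional:** tabulate adverse events by arm and spinal analgesia, with skin and thermal events shown separately.

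**Cost:** a brief bedside check, a few lines of protocol text and two recorded items. Heat will start later in some women with analgesia. A start after 2.5 hours leaves less than a full session before the cut-off, which may slightly dilute the effect, so the analgesia subgroup should be read with the recorded start times. If the standard procedure already contains the check, the change is only to write it into the protocol and settle the analysis status.

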### **2.3.5.3 Subject withdrawal**

On request, the enrolled subjects can withdraw from the clinical trial at any stage of the study.

### **2.3.5.4 Subject drop-out and discontinuation**

- (1) Implementation of rescue due to postpartum hemorrhage, eclampsia, or other obstetric conditions;
- (2) Change of vaginal delivery to cesarean section;
- (3) Infection during delivery;
- (4) Indwelling catheter and the need to use diuretics due to disease within 6 hours after delivery;
- (5) Degree III laceration above the perineal fissure;
- (6) Neonatal transfer after birth;
- (7) The investigator can terminate the subject from continuing the clinical trial at any stage, if the investigator deems that the risks of continuing the clinical trial outweigh the benefits;
- (8) Subject's poor compliance to this trial.

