## **2.6 Interventions**

### **2.6.1 Control group**

The participants in the control group received routine postpartum care, including the observation of their vital signs (blood pressure, heart rate, respiratory rate, temperature and oxygen saturation of blood), the monitoring the amount of vaginal bleeding and discharge of lochia, the palpation of their fundus, cleansing of their vulva and an early interaction with their newborns.

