## 8. Safety Analysis

Adverse event listings will be generated and events will be classified according to seriousness, treatment relationship and resolution. Descriptive statistics (numerical measures, frequency tables) will be used to summarize the occurrence of adverse events and serious adverse events by intervention group.

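### Haemorrhage rescue and investigator risk decisions count as drop-out of randomised women, with no split by timing or between stopping the compress and ending follow-up, so exposure-related events could be under-counted and outcomes lost

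*Supplement*

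**What the plan says.** **Leaving the trial.** Protocol 2.3.5.4 lists eight reasons for drop-out and discontinuation. Rule (1) is "Implementation of rescue due to postpartum hemorrhage, eclampsia, or other obstetric conditions", with no time limit. Rule (7) begins "The investigator can terminate the subject from continuing the clinical trial at any stage" and makes this depend on a judgement that risk exceeds benefit. They stand beside caesarean section, third-degree laceration and poor compliance. No rule says whether data collection continues afterwards.

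**Exposure.** Figure 1 places randomisation at enrolment, before allocation. Protocol 2.6.2 states: "In addition to routine postpartum care, the participants in the intervention group were administered a 4-hour acupoint hot compress". The first application begins within half an hour of delivery, at the umbilicus, sacrum and soles. The later ones are at 24 and 48 hours.

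**Bleeding.** Routine care in protocol 2.6.1 includes "the monitoring the amount of vaginal bleeding and discharge of lochia". Both arms receive that care. Bleeding is not in the Figure 1 assessments, the baseline list (2.7), the outcomes (2.8) or any SAP analysis.

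**Safety data.** Protocol 2.9 says "AEs will be monitored and recorded in detail throughout the whole study period". SAP 8 says "Adverse event listings will be generated and events will be classified according to seriousness, treatment relationship and resolution", followed by a descriptive summary by arm. Protocol 6 plans a data monitoring committee but does not describe its remit.

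**Analysis set.** Protocol 7 and SAP 1 specify intention-to-treat in all randomised women. Item (2) of protocol 11 calls the analysis per protocol. SAP 3 assumes data are missing at random and uses multiple imputation.

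**The concern.** A woman can be randomised, start the compress, need rescue for haemorrhage, and be classed as a drop-out. An event that might be a consequence of exposure then serves as the reason for leaving. Two things are at stake.

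The first is safety. Nothing says that a rule (1) rescue or a rule (7) termination must also be entered as an adverse event. If some are not, the by-arm summary is incomplete. The investigator who makes a rule (7) decision in an open-label trial may know the arm, so the omission need not be equal in the two arms.

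The second is efficacy. If leaving ends data collection, the later assessments are lost for women selected by an event after randomisation. Those include catheter use up to 72 hours (part of the primary outcome), pain and lactation to 76 hours, and the depression scale at 76 hours.

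**Working it through.** **Step 1: can rules (1) and (7) apply after exposure starts?** Rule (1) gives no time and rule (7) applies at any stage. The list is not confined to delivery: rule (4) runs to 6 hours after it, and rule (8) concerns compliance with the trial. Follow-up ends at 76 hours and the first compress starts by 0.5 hours, so at least 75.5 of the 76 hours follow its scheduled start. Rules (2), (3), (5) and (6), however, concern events around delivery, and rule (1) also covers haemorrhage before any compress. The text allows both timings and distinguishes neither.

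**Step 2: is the event certain to reach the safety table?** It does so only if recorded as an adverse event. The documents do not define the term, do not say that rescue or risk-based termination qualifies, and do not say that collection continues after discontinuation. No SAP table gives discontinuations by arm and reason.

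**Step 3: does the analysis set protect against loss?** SAP 1 keeps all randomised women, but an analysis set cannot supply data that were not collected. If the per-protocol statement in protocol 11 governs, these women may be left out altogether.

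**Step 4: size.** The plan has no haemorrhage figure to reproduce. Its 600 per group (protocol 2.4) is used here only as the number randomised. Recomputing it from the stated inputs (25.7% v 7.7%, one-sided 0.025, power 80%):

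n = [1.96 × √(2 × 0.167 × 0.833) + 0.8416 × √(0.257 × 0.743 + 0.077 × 0.923)]² / 0.18² = (1.034 + 0.431)² / 0.0324 = 66.2, so 67 per group; 67 / 0.8 = 84 after 20% drop-out.

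The 600 does not follow from these inputs, but nothing below depends on its derivation.

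Illustration, with all rates **assumed**: control-arm rescue rate p from 1% to 5%, doubled in the treated arm, two-sided 5% test.

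Power = Φ{[p − 1.96 × √(2 × 1.5p × (1 − 1.5p) / n)] / √([p(1 − p) + 2p(1 − 2p)] / n)}

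- p = 1%, n = 600: (0.01 − 1.96 × 0.00702) / 0.00701 = −0.54, power 30%.
- p = 5%, n = 600: (0.05 − 1.96 × 0.01521) / 0.01514 = 1.33, power 91%.

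| Control v treated | Women at 600 per arm | Power at 600 | Power at 500 |
|---|---|---|---|
| 1% v 2% | 6 v 12 | 30% | 26% |
| 2% v 4% | 12 v 24 | 53% | 46% |
| 3% v 6% | 18 v 36 | 71% | 63% |
| 5% v 10% | 30 v 60 | 91% | 85% |

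The 500 column takes 10 remaining centres × 50, since protocol 11 reports two of the 12 lost, and assumes no replacement.

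If every event were counted, the risk difference ± 1.96 SE at 600 per arm would be:

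- 1% v 2%: 1.0 ± 1.96 × 0.70 points, or −0.4 to 2.4.
- 5% v 10%: 5.0 ± 1.96 × 1.51 points, or 2.0 to 8.0.

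The planned drop-out is 0.20 × 600 = 120 per arm. An excess of 6 to 30 women fits inside it.

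**The case against.** The strongest reply is that the plan already covers this. Adverse events are recorded for the whole study and summarised by arm, the SAP set is all randomised women, and a data monitoring committee is planned. Protocol 4 speaks of adverse events whether or not related to the study. Being a drop-out reason does not stop an event from being an adverse event. This stands against one stronger reading: a reader might infer that a bleeding harm would go wholly unseen. The documents do not support that, because a haemorrhage recorded as an adverse event would appear by arm. What remains is that nothing requires the recording.

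Three further inferences also fail.

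- **That rule (1) removes women after exposure.** It is silent on timing, and many of its cases may precede any compress.
- **That bleeding data are already in hand.** Protocol 2.6.1 describes bedside monitoring only. No text says the amount is measured in a standard way or entered on the case report form.
- **That heat increases bleeding.** No passage suggests it, and the statements in protocol 2.9 and 4 that no events have been reported concern past use of the device. They show neither harm nor under-recording in this trial.

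It is also fair to say that 20% drop-out is a planning allowance, not a level below which losses go unexamined. The protocol commits to CONSORT. Its flow chart is not visible in the copy reviewed, so whether it shows losses by arm cannot be judged.

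**Conclusion.** The point holds as a gap in the rules and should be mended; it is not evidence of harm. As written, 2.3.5.4 lets a randomised woman leave because of an event that exposure could have affected, without recording when the event arose or keeping her in follow-up. Events may be under-counted in SAP 8 and outcomes lost, despite the safety recording that is planned. The conflict between per-protocol and intention-to-treat wording makes the loss more likely and must be reconciled.

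The size is unknown. Under assumed control rates of 1% to 5%, a doubling concerns 6 v 12 to 30 v 60 women at 600 per arm. Even complete counting would give power of only about 30% to 91%. A full table would therefore not guarantee detection, and at the lower rates an incomplete one would weaken a comparison that is already imprecise.

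**What to change.** 1. **Protocol 2.3.5.4.** Separate discontinuing the compress from leaving the study. State that a randomised woman who meets rule (1) or (7) after the first compress, or after the matching time in controls, stays in follow-up to 76 h for adverse events and outcomes unless she withdraws consent. When the compress is stopped remains the sponsor's clinical decision.
2. **SAP 8.** Count every haemorrhage rescue and every rule (7) termination as a safety event. Report these, and all discontinuations, by arm, reason and timing relative to the first compress, in all randomised women, as n/N with risk difference and 95% CI. Report the amount of bleeding by arm only if it is recorded on the case report form.
3. **Protocol 7, protocol 11 and SAP 1.** Reconcile the per-protocol and intention-to-treat statements.

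The cost is some wording, a few extra follow-up contacts, mostly in women still in hospital, and one safety table. If enrolment is over, the table can still be built as far as drop-out reasons and times were recorded, but follow-up that was not done cannot be recovered and should be reported as missing by arm.
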